**Fig. 1 Fig1:**
[figure not shown]
Appointment schedule

### Study setting

The trial will be conducted at a dedicated clinical trials facility at University Hospital Geelong, Victoria. This space includes appropriate consultation spaces and on-site equipment for intervention delivery and the collection of biological samples. This study will consist of 10 study appointments, six of which are in-person and four via telehealth (see Table 1 and Fig. 1).

The collection of blood samples will be performed by a qualified research nurse or phlebotomist, where markers of cardiovascular and metabolic disease risk (e.g. lipids, HbA1c, and blood glucose) will be assayed. Additional blood samples will be collected and transported to the Geelong Centre for Emerging and Infectious Disease (GCEID) laboratories in Geelong for additional blood analyses and long-term storage.

Stool samples will be collected by participants at home using a Microba (Queensland, Australia) stool sampling kit. Participants will then return the completed kits to research personnel at their study appointments. These stool samples will be de-identified (marked with a participant code only) and sent to Microba for metagenomic analyses.

### Study population

This study aims to recruit 15 participants, aged 18 to 65 years of age, with a DSM-5 diagnosis of MDD (confirmed by a psychiatrist using the Structured Clinical Interview for DSM-5 (SCID-5) MDD module) [60] of moderate-to-severe range (defined as a Montgomery Asberg Depression Rating Scale (MADRS) score of greater than or equal to 20) [61]. Eligibility criteria are outlined in Table 2. The recruitment strategies are outlined in Table 3. Once participants have given consent and been screened and determined eligible for entry into the study, they will be randomised to either active FMT enema or placebo enema, which will be delivered on four consecutive days in the first week of the study. Participants will then be followed up fortnightly for 8 weeks, with a final appointment at week 26 to capture long-term safety data. The participant schedule and study outcomes are summarised in Table 1 and Fig. 1

**Table 2 Tab2:** Eligibility criteria of participants enrolled in the Moving Moods Pilot Study

Inclusion criteria:	
1. Adults (age 18–65 years)	
2. MDD according to Structured Clinical Interview for DSM-5 (SCID-5) MDD module	
3. Moderate-to-severe score on MADRS (i.e. score of greater than or equal to 20)	
4. Stable treatment (i.e. pharmacological and psychological) for 1 month prior to commencing trial	
Exclusion criteria:	
1. Active suicidality (a MADRS suicide item score of 5 or 6)	
2. Use of probiotics, antibiotics, or any experimental drug in the 1 month prior to study entry	
3. Serious gastrointestinal conditions (including active inflammatory bowel disease, bowel cancer, or a history of major bowel surgery, but not including IBS, chronic diarrhoea, or constipation)	
4. Pregnancy or breastfeeding (pregnancy will be excluded using a urine pregnancy test at baseline)	
5. Major comorbid psychiatric disturbances including bipolar disorder, a primary psychotic illness, obsessive-compulsive disorder, anorexia nervosa, or bulimia nervosa	
6. Active substance-use disorder, defined as a score of 6 or greater on the brief Drug Abuse Screening Test (DAST-10), and/or a score of 16 or greater in the Alcohol Use Disorders Identification Test (AUDIT)	
7. Inability to read and understand the participant information and informed consent form	
8. Patients with a history of severe anaphylactic or anaphylactoid food allergy	
9. A condition that could jeopardize the safety or rights of the subject, make it unlikely for the subject to complete the study, or confound the results of the study

**Table 3 Tab3:** Recruitment strategies

1. Flyers will be displayed in the waiting rooms of key recruitment sites	
2. Advertisements through social media	
3. Clinicians at key recruitment sites will advise of appropriate patients for the trial	
4. Trial Facts or HealthShare, which are services connecting patients and doctors, will identify appropriate participants for the trial. These will be utilised only if the above strategies are insufficient.	

### Follow-up appointments

Follow-up appointments will be conducted by a qualified member of the research team. The data collected at these assessments are summarised in Table 1.

### Outcomes

The study appointment schedule is detailed in Table 1. Primary, secondary, and exploratory outcomes are described below.

### Primary outcome measures

The primary outcomes for this study are (1) the feasibility and (2) safety of FMT as an adjunctive treatment for MDD in adults. The study outcomes, participant appointment schedule, and study timeline are outlined in Table 1 and Fig. 1.

Feasibility will be considered as a composite outcome, measured by the following:The ability to meet recruitment targets (measured by recruitment logs, comparing actual recruitment against projected targets)Participant retention and completion rates (measured by attrition rates and completeness of data)Adherence to intended protocol (measured by completion of intervention as planned, missed appointments, technical difficulties arising, and completeness of study data)Participant acceptability (measured using the TransCelerate Study Participant Feedback Questionnaire, plus the addition of questions designed specifically for this study)Robustness of study methodology, including effectiveness of blinding (measured qualitatively based on feedback from researchers throughout and at the conclusion of the study, and a participant and researcher survey to assess blinding)

Safety of FMT as an adjunctive treatment in adults will be measured by an assessment of adverse events. These data will be collected through direct observations by the study nurse during administration of the intervention, and via participant reporting during the intervention and each appointment thereafter (measured at weeks 0, 2, 4, 6, 8, and 26). Participants will also be encouraged to contact the research team at any time to report adverse events outside of study appointments.

### Secondary outcome measures

The secondary outcome measure of this study is changes in gut microbiota composition and functional potential, which will be measured via the following:The degree of change in gut microbiota composition and functional potential in recipients, which will be assessed by observing changes in gut microbiota composition (alpha diversity, beta diversity, differential abundance of species) and functional potential at 2- and 8-weeks post-intervention compared with baseline.The degree of microbial ‘engraftment’: degree to which the changes in gut microbiota composition and functional potential of recipients are concordant with the gut microbiota profiles of the donor stool post-active FMT and compared with placebo enema.Donor vs recipient at baseline (0 weeks)Donor vs recipient at 2 weeks (active FMT compared with placebo group)Donor vs recipient at 8 weeks (active FMT compared with placebo group)

### Exploratory outcome measures

The following data will be collected as part of the primary feasibility outcome, described above. However, given the small sample size, it is expected that the study will be underpowered to measure significant changes in any of the following outcome measures. As such, these outcomes are considered “exploratory”. To avoid type I error inflation due to multiple comparisons, we aim to only record summary descriptions of these clinical outcomes. These exploratory outcomes are as follows:Between-group differential change from baseline and weeks 2, 4, 6, and 8 in mental health symptoms as measured by the Montgomery-Asberg Depression Rating Scale (MADRS) and the Depression-Anxiety Stress Scale (DASS)Between-group differential change from baseline and weeks 2, 4, 6, and 8 in quality of life as measured by the Assessment of Quality of Life-8 Dimension (AQoL-8D); this scale also allows the calculation of preference-based outcomes also known as utilities. Utility values will be used to calculate quality adjusted life years (QALYs), a common metric used in economic evaluationsBetween-group differential change from baseline and weeks 2, 4, 6, and 8 in sleep as measured by the Pittsburgh Sleep Quality IndexBetween-group differential change from baseline and weeks 2, 4, 6, and 8 in level of function as measured by the Sheehan Disability ScaleBetween-group differential change from baseline and weeks 2, 4, 6, and 8 in gut symptomatology as measured by the Gastrointestinal Symptom Rating Scale (GSRS)Between-group differential change from baseline and weeks 2 and 8 in in blood biomarkers of neurogenesis (e.g. brain-derived neurotrophic factor)Between-group differential change from baseline and weeks 2 and 8 in cardiometabolic blood parameters (e.g. random lipid profile, random blood sugar levels and HbA1c)Between-group differential change from baseline and weeks 2 and 8 in metabolic and cardiovascular risk factors assessed via physical exam, including heart rate, blood pressure, height, and weightCost effectiveness will be assessed from both health sector and societal perspectives. The cost of FMT via enema will be estimated and added to the cost of lost productivity and health care resources utilised by participants over the course of the trial using the Resource Utilization Questionnaire (measured at weeks 0 and 8)Between-group differential change from baseline and weeks 2, 4, 6, and 8 in self rated overall improvement assessed using the Patient Global Impression of ChangeBetween-group differential change from baseline and weeks 2 and 8 in inflammation (e.g. macrophage inhibitory factor, interleukins 1b, 1ra, 6 and 10, soluble CD14, and high sensitivity C-reactive protein) will be measured in plasma and/or serum using immunoassays (e.g. solid phase sandwich ELISA assay)Between-group differential change from baseline and weeks 2 and 8 in gut permeability (e.g. lipopolysaccharide binding protein and zonulin) will be measured in plasma and/or serum using immunoassays (e.g. solid phase sandwich ELISA assay)

### Feasibility targets

Table 4 outlines pre-specified targets identified by the research team as a minimum standard that would indicate that the study design was feasible. These targets will also assist the study team to identify aspects of the trial that may need to be amended to improve future, large-scale trials.

**Table 4 Tab4:** Feasibility targets

Target area	Feasibility target
Recruitment	Successful enrolment of *n* = 15 participants across a 6-month active recruitment period
Retention	A minimum of *n* = 10 participants to complete study until the 8-week primary endpoint (i.e. a 33% attrition rate).
Adherence to protocol	Participants should: 1) Receive two of the total four enemas 2) Attend their baseline, week 2 and week 8 appointments 3) Provide baseline and week 2 stool samples
Safety	Nil severe and/or serious adverse events rated as likely due to study intervention in the active FMT group.
Adequacy of blinding	The best achievable outcome for adequacy blinding is participants and researchers correctly guessing allocation at a rate of 50% (the rate due to chance). Whilst we are not likely to be statistically powered to measure this outcome, we aim to reach an outcome approaching 50%.

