**Discussion:**

Modification of the microbiota-gut-brain axis via FMT is a promising potential treatment for MDD, but there are no published rigorous clinical trials evaluating its use. If this study finds that our FMT strategy is safe and feasible, a larger fully powered RCT is planned. Further high-quality research in this field is urgently needed to address unmet need.

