## Methods

### Objectives

The primary objectives for this study are to evaluate the feasibility and safety of FMT as an adjunctive treatment for MDD in adults. The secondary objective is to evaluate the impact of enema-delivered FMT on gut microbiota compared with a placebo enema in adults with MDD. As this study is not powered to evaluate efficacy, exploratory objectives include any changes observed in depression and anxiety symptoms, sleep, quality of life, level of function, gut symptomatology, blood biomarkers of neurogenesis, gut permeability, inflammation, and cardiometabolic parameters following delivery of FMT via enema compared with a placebo enema in adults with depression.

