### Study design

This study is an 8-week, triple-blind, 2:1 parallel group, randomised controlled pilot trial (*n* = 15), of enema-delivered FMT (*n* = 10) compared with a placebo enema ( *n*= 5) in adults with moderate-to-severe MDD. There will be a further 26-week follow-up for safety data.

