### Sample size, power, and statistics

#### Feasibility analysis

As this is a feasibility study, it is not designed or powered to evaluate statistically significant changes in any of the parameters being assessed. Therefore, a qualitative synthesis of feasibility data will be reported.

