### Plans for sharing and/or future use of data and/or follow-up research

This project is inter-departmental and interdisciplinary. Data will be shared between the respective groups involved in its execution. There are plans for future use of the data and product developed in this project. If this project proves to be feasible, our group intends to use the same or similar enema FMT product and protocol and test its efficacy in a larger randomised controlled trial powered to detect changes in depressive symptomatology.

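### Meeting the safety target in about 10 active participants supports 'no signal seen', not the finding of 'safe' that the abstract attaches to the larger trial

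*Protocol article*

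**What the plan says.** The Objectives section of the protocol article puts safety level with feasibility: "The primary objectives for this study are to evaluate the feasibility and safety of FMT as an adjunctive treatment for MDD in adults". Under Primary outcome measures, "Safety of FMT as an adjunctive treatment in adults will be measured by an assessment of adverse events", with collection at weeks 0, 2, 4, 6, 8 and 26. The Study design section gives the size: "randomised controlled pilot trial (*n* = 15), of enema-delivered FMT (*n* = 10) compared with a placebo enema", with 5 participants on placebo.

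The only pre-specified safety criterion in the article is the safety row of Table 4 (Feasibility targets): "Nil severe and/or serious adverse events rated as likely due to study intervention in the active FMT group". The text introducing the table describes its targets "as a minimum standard that would indicate that the study design was feasible".

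The article describes the route to the larger trial in two ways. The abstract says: "If this study finds that our FMT strategy is safe and feasible, a larger fully powered RCT is planned". The section on plans for sharing and future use says: "If this project proves to be feasible, our group intends to use the same or similar enema FMT product and protocol", and goes on to testing efficacy in a larger trial. The main Discussion twice makes the larger trial depend on feasibility, without a separate finding of safety.

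On precision, the Feasibility analysis section says of the study that "it is not designed or powered to evaluate statistically significant changes in any of the parameters being assessed", and plans a qualitative synthesis. The article states neither an unacceptable event rate nor an interval for the safety result.

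**The concern.** A primary outcome with one pass criterion invites the reader to treat a pass as the answer to the primary question. Here the criterion is zero events, of one attribution grade, in one arm of 10. The abstract allows the study to find the FMT strategy safe and makes the larger trial follow from that. If the target is met, nothing in the article tells the reader how large an event rate remains possible.

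The existing caveats do not fill this gap. The Feasibility analysis section disclaims power to detect significant changes. The limitation in the Discussion ties the small sample to the secondary outcomes, then says the study was designed to evaluate its primary aim of feasibility. Neither says that passing the safety target leaves safety unproven.

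At stake is the conclusion the trial may draw on one of its two primary outcomes, and the assurance on safety that is carried into a larger trial.

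**Working it through.** **Figures in the plan.** The article gives no precision or error rate for the safety target, so there is none to reproduce. Its simple figures agree: 15 × 2/3 = 10 active, 15 × 1/3 = 5 placebo, and 5/15 = 33.3% tolerated attrition.

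**Inputs.** n = 10 active (Study design). Pass rule: 0 qualifying events in the active arm (Table 4). A qualifying event is a severe or serious event rated as likely related. The true per-participant rate p is not given, so a range is shown.

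**1. What 0/10 leaves open.** The exact upper bound for 0/n is 1 − 0.05^(1/n) one-sided and 1 − 0.025^(1/n) two-sided.
- One-sided 95%: 1 − 0.05^(1/10) = 25.9%.
- Two-sided 95%: 1 − 0.025^(1/10) = 30.8%.

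**2. How often the target is met.** P(0 events) = (1 − p)^10.

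| True rate of qualifying events | Chance the target is met |
|---|---|
| 1% | 90.4% |
| 2% | 81.7% |
| 5% | 59.9% |
| 10% | 34.9% |
| 15% | 19.7% |
| 20% | 10.7% |
| 30% | 2.8% |

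The chance is one half at p = 1 − 0.5^(1/10) = 6.7%. The target is met more often than not only below that rate.

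**3. Effect of counting only one attribution grade (assumption).** Suppose half of truly related severe or serious events were rated as likely. A true rate of 10% then passes with probability (1 − 0.10 × 0.5)^10 = 59.9%, and a true rate of 20% with probability (1 − 0.20 × 0.5)^10 = 34.9%. The one half is illustrative and does not come from the article.

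**4. Effect of the number followed.** Table 4 accepts 10 completers of 15 at week 8 and does not split them by arm. If all five losses were on placebo, 10 active participants remain; if all were active, 5 remain. For 0/5 the bounds are 1 − 0.05^(1/5) = 45.1% one-sided and 1 − 0.025^(1/5) = 52.2% two-sided. Depending on who is followed, the one-sided bound for a pass therefore lies between 25.9% and 45.1%.

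**5. Scale.** For zero events to exclude a rate p at one-sided 95%, n must be at least ln(0.05)/ln(1 − p): 29 for 10%, 59 for 5% and 299 for 1%. A pilot of this size is not expected to reach these numbers. They show how far a pass is from demonstrating safety.

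**The case against.** The strongest defence is that Table 4 is not a test of safety. The article presents it as a minimum standard for the design. The safety outcome itself is wider: all adverse events are collected to week 26 with no attribution filter. Under Safety requirements, an independent monitoring board is told promptly of any severe or serious event, in either arm and whatever its rating, and decides whether to pause recruitment or halt the study. The trial is openly unpowered, commits to the CONSORT extension for pilot trials, and in three places makes the larger trial follow feasibility alone. Tables by arm and exact intervals are commonly left to an analysis plan.

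Most of this stands. It means the target need not change and participants are not left unprotected by it. It does not settle what a pass may be taken to mean. If Table 4 is only a feasibility minimum, the article has no criterion for the safety half of the abstract's condition.

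A reader might infer that the target is easily met by an unsafe product. The article does not support that. It gives no unacceptable rate, and the target is met only 10.7% of the time at a true rate of 20% and 2.8% at 30%, so a high rate of qualifying events would usually be caught. A reader might also infer that worsening mood or suicidality is especially unlikely to be attributed to the intervention. Nothing in the article says so; suicidality is recorded at baseline and weeks 2, 4, 6 and 8, and assessors are blinded. Making lower-rated events fail the target would trade missed events for false failures, and the article gives no basis for choosing between them.

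**Conclusion.** The point holds as one about the conclusion, not as a defect in how safety is monitored. Meeting the target supports the statement that no safety signal was seen. It does not support a finding that FMT is safe in this population, because 0/10 leaves a true rate of qualifying events up to 25.9% (one-sided 95%) or 30.8% (two-sided 95%) unexcluded, and the target is passed 60% of the time at 5% and 35% at 10%.

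These figures assume independent participants, all 10 active participants followed, and events that meet the target's own definition. With fewer followed the bound is wider, up to 45.1% one-sided in the extreme case of 5. The article's descriptions of what leads to the larger trial also differ and should be reconciled. This is a modest but worthwhile correction, since it changes what may be concluded on a primary outcome at very little cost.

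**What to change.** 1. Keep the safety row of Table 4 as a minimum feasibility standard, and add a sentence that meeting it means no safety signal was observed and does not establish safety.
2. Report severe and serious events by arm regardless of attribution, showing those rated possibly related alongside those rated likely. With 10 and 5 participants this is descriptive only.
3. Give the exact upper 95% bound for qualifying events in the active arm, stating whether it is one- or two-sided, with the number actually followed to week 8 and to week 26 as the denominators. Do not quote a fixed 26% unless all 10 were followed.
4. Reword the abstract so that the larger trial is planned if the feasibility targets are met and no safety signal is seen. Use the same condition in the data-sharing section and in both places in the Discussion.

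The cost is a slightly less favourable stated conclusion and a little more tabulation. The adverse-event data are already to be collected in both arms, so no visits, participants or new data are needed.

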**Methods and design:**

This protocol describes an 8-week, triple-blind, 2:1 parallel group, randomised controlled pilot trial (*n* = 15), of enema-delivered FMT treatment (*n* = 10) compared with a placebo enema (*n* = 5) in adults with moderate-to-severe MDD. There will be a further 26-week follow-up to monitor longer-term safety. Participants will receive four FMT or placebo enemas over four consecutive days. The primary aims of the study are to evaluate feasibility and safety of FMT as an adjunctive treatment for MDD in adults. Changes in gut microbiota will be assessed as a secondary outcome. Other data will be collected, including changes in depression and anxiety symptoms, and safety parameters.

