Medical variables	Change in medications, vaccines, illness, etc			✓				✓	✓	✓	✓	
General health and functioning	Patient Global Impression of Change Sheehan Disability Scale Sleep (Pittsburgh Sleep Quality Index) Quality of Life			✓				✓	✓	✓	✓	
Study appointments continued.												
Changes of circumstance	Medication changes questionnaire			✓				✓	✓	✓	✓	
Cost analysis	Resource Utilisation Questionnaire			✓							✓	
Physical examination	Height (stadiometer) Weight (scales) Blood pressure (sphygmomanometer) Heart rate (sphygmomanometer)			✓				✓			✓	
Blood samples	Whole blood by research nurse/ACL			✓				✓			✓	
Stool samples	Microba stool collection kits			✓				✓			✓	
Feasibility data												
Tolerability	Adverse events			✓	✓	✓	✓	✓	✓	✓	✓	✓
Adequacy of blinding	Participant questionnaire							✓				
Adherence	Monitoring questionnaire completion and appointment attendance throughout the study period			✓	✓	✓	✓	✓	✓	✓	✓	
Acceptability	Study Participant Feedback Questionnaire Specific questions pertaining to study intervention			✓				✓			✓	
Researcher/trial feasibility data												
Recruitment	Monitoring of recruitment rates by study staff throughout trial period			✓	✓	✓	✓	✓	✓	✓	✓	
Retention	Monitoring of trial attrition by study staff throughout trial period			✓	✓	✓	✓	✓	✓	✓	✓	

The study schedule allows for flexibility for all or parts of each appointment to be conducted by telehealth if this is preferable to the participant or required for other reasons

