### Trial allocation, sequence generation, and blinding

Allocation to treatment arms will be randomly assigned in a 2:1 ratio using permutated block randomisation. Unblinded researchers independent to the study team, utilising a simple randomisation method, will develop the randomisation sequence and assign participants to study arms. The unblinded researchers will allocate and package enema kits sequentially, and packaging will be identical to conceal treatment allocation and blinding. The study staff, investigators, trial biostatistician, nurses delivering the enemas, and participants will be blinded to group allocations.

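### Table 4 takes 50% correct guesses as the chance rate, but under 2:1 allocation the chance rate depends on how people guess and runs from 33% to 67%

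*Protocol article*

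**What the plan says.** The Study design section describes an "8-week, triple-blind, 2:1 parallel group, randomised controlled pilot trial" of "enema-delivered FMT (*n* = 10) compared with a placebo enema", and the abstract gives the other arm as "compared with a placebo enema (*n* = 5". The section on allocation and blinding repeats the ratio: "Allocation to treatment arms will be randomly assigned in a 2:1 ratio using permutated block randomisation".

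Table 4 (Feasibility targets) sets minimum standards for calling the design feasible. For blinding, the ideal is "participants and researchers correctly guessing allocation at a rate of 50% (the rate due to chance". The same cell concedes that power for this outcome is unlikely and then says "we aim to reach an outcome approaching 50" per cent. It gives no tolerance around that figure and no expected split of guesses.

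On data collection, Primary outcome measures lists "a participant and researcher survey to assess blinding", alongside researcher feedback during and at the end of the study. In Table 1 the blinding row names one instrument, "Participant questionnaire", ticked at week 2. The separate researcher block of Table 1 holds only recruitment and retention.

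**The concern.** Fifty per cent is the chance rate for a two-way guess when the arms are equal in size, whatever people guess. With unequal arms this no longer holds: anyone who leans towards the larger arm is right more often than half the time without knowing anything. The article states the equal-arm figure without qualification in a trial that is not equal-arm.

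Feasibility is a primary outcome, blinding is a named part of it, and Table 4 is the standard against which it will be read. With a misplaced benchmark, a harmless result can look like a failure of blinding, and a result that deserves a closer look can seem ideal.

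**Working it through.** **Inputs.** Active 10 and placebo 5, so the active share is a = 10/15 = 2/3 (Study design; abstract). Stated chance rate 50% (Table 4). The share guessing active, g, is not given and is varied from 0 to 1. Guesses are assumed to be active or placebo only, because the article does not describe a third option.

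**Formula.** Intact blinding means that the guess is independent of the arm, so

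P(correct) = a·g + (1 − a)·(1 − g).

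**Reproducing the plan's figure.** With a = 1/2, P(correct) = g/2 + (1 − g)/2 = 50% for every g. With a = 2/3, P(correct) = 1/3 + g/3, which is 50% only at g = 0.5. The stated figure therefore needs either 1:1 allocation or an even split of guesses.

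| g (share guessing active) | Chance rate at 2:1 |
|---|---|
| 0 | 33.3% |
| 0.25 | 41.7% |
| 0.5 | 50.0% |
| 2/3 (guesses follow the allocation odds) | 55.6% |
| 0.75 | 58.3% |
| 1 | 66.7% |

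**An uninformative result that looks bad.** If all 15 guess active, 10/15 = 66.7% are correct. The chance rate at g = 1 is also 66.7%, so the excess is zero. Less extreme guessing can give the same count: under intact blinding (convolving Binomial(10, g) with Binomial(5, 1 − g)), 10 or more of 15 are correct with probability 0.26 at g = 2/3, against 0.15 at g = 0.5.

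**A result that looks ideal but is above its own chance rate.** Suppose 5/5 on placebo and 3/10 on active guess correctly.
- Pooled rate: 8/15 = 53.3%.
- Guesses of active: 3 + 0 = 3, so g = 3/15 = 0.2.
- Implied chance rate: 1/3 + 0.2/3 = 40%.
- Excess: 53.3 − 40.0 = 13.3 percentage points.
- Check: the excess equals 2a(1 − a) times the difference between arms in the share guessing active, 2 × (2/3) × (1/3) × (3/10 − 0/5) = 0.133.

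This excess is not evidence of unblinding. Fisher's exact test on these guesses gives p of about 0.5, and the exact 95% interval for 8/15 runs from 27% to 79%.

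**Why arm-specific indices must be read together.** With no third option, an arm's Bang index is 2 × (share correct) − 1. If everyone guesses active, the indices are +1 (active) and −1 (placebo). Neither is near 0, although guesses carry no information; their sum is 0. In the 5/5 and 3/10 example they are +1 (placebo) and −0.4 (active), with sum 0.6.

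**The case against.** The strongest reply is that no pass/fail rule is there to break. The target is only to come close to 50%, no tolerance is set, low power is conceded, and Feasibility analysis promises a qualitative synthesis. This stands. A reader might infer that perfect blinding would fail the target, or that a poor placebo would pass it; the article contains no threshold that would make either happen.

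Second, 50% is a legitimate chance rate if guesses split evenly, and for g between 0.25 and 0.75 the true rate stays between 42% and 58%. One guess in 15 moves the result by 6.7 points, so 50% and 56% cannot be told apart here. This limits the size of the point but does not make the unqualified statement correct.

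Third, a reader might infer that one arm could be completely unblinded and still meet the target. That is too strong. Near-50% totals with one arm fully correct arise only for placebo; a fully correct active arm gives at least 10/15 = 66.7%. The placebo case also needs 7 or 8 of 10 active recipients to guess wrongly, which fits a general lean towards guessing placebo. Masking of one arm by the other comes from pooling and can occur at 1:1 as well; what 2:1 adds is the shifting chance rate.

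Fourth, the article does plan researcher feedback and a researcher survey. It would be wrong to say that these data will not be collected; the gap is only in Table 1.

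Finally, the article does not say that the later trial will reuse this placebo. It says that, if this trial proves feasible, the group intends to use the same or a similar FMT product and protocol.

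**Conclusion.** The point holds in a limited form. The 50% benchmark is wrong as an unqualified statement under 10:5 allocation: the chance rate is 1/3 + g/3, from 33% to 67%, and is 56% if guesses follow the allocation odds. The effect is on how one feasibility standard is read, so the importance is moderate. No inferential analysis rests on the figure.

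The conclusion assumes two-way guesses and the planned 10:5 split among those whose allocation is guessed. For researchers it assumes one guess per participant. The article does not say whether participants are told the ratio, so no single value of g is put forward as the likely one.

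Separately, Table 1 and the outcome text disagree on whether researchers are surveyed about blinding. This is a small inconsistency to reconcile.

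**What to change.** 1. In Table 4, replace 50% as the chance rate with the rate implied by the observed guesses: 1/3 + g/3 for 10:5. With nA active and nP placebo participants whose allocation was actually guessed, use [nA·g + nP·(1 − g)]/(nA + nP).
2. Report guesses by arm and read the two arms together, for example as the share guessing active in each arm, or as both arm-specific blinding indices side by side. Do not require each index to be near 0, because that would flag intact blinding whenever most people lean the same way.
3. Add the researcher survey, with its timing, to Table 1 so that it agrees with Primary outcome measures and Table 4.

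The cost is one reworded table cell, one added table entry and slightly more descriptive reporting, with no extra patients or staff.
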